### Outcomes

#### Primary

The primary outcome will be headache impact, measured using the Headache Impact Test (HIT-6), requiring a decrease of at least 6 points in the headache-related impact measured by the HIT-6 [34], which will be applied at the baseline, and at four, eight, and 12 weeks of treatment, and at follow-ups at 1, 2, and 4 months.

#### Secondary

The secondary outcomes will be as follows: frequency of migraine, intensity of migraine, pressure pain threshold, cervical range of motion, cervical muscle strength, upper cervical mobility, cervical muscle performance, disability related to neck pain, cutaneous allodynia, kinesiophobia, pain-related catastrophizing, quality of life, and perception of clinical change. All secondary outcomes will be measured at the fourth, eighth, and twelfth week. The frequency and intensity of migraine will also be evaluated at the 1-, 2-, and 4-month follow-ups.

### Sample size

The sample size was calculated for the primary outcome, the HIT-6. It was based on a mean reduction of six points and a standard deviation of 6.03, while adopting a significance level (α) of 0.05 and power of 90%. We estimated 21 individuals per group, and considering a 15% loss to follow-up, 25 individuals per group will be required. Therefore, 75 individuals will be included in this clinical trial. An effect size of ≥ 6 points at HIT-6 is the minimum clinically important difference (MCID) for this scale [34]. The standard deviation was derived from a sample of nine volunteers from our database of previous studies.

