Craniocervical exercises may also be beneficial for patients with migraine, as they have proven to be effective in individuals with neck pain and other headaches associated with cervical spine impairments [20–22]. However, no systematic review has determined its effectiveness in this population. Considering the decrease in cervical muscular performance [23, 24] and cervical muscle resistance [25] in women with migraine, these patients could also benefit from associated exercise programs. It has already been proven that different musculoskeletal and functional dysfunctions accompany migraine headaches. Furthermore, it has been suggested that patients with migraine could benefit from multimodal treatment that includes relaxation techniques, manual therapy, stretching, and active neck exercises, in addition to therapeutic pain neuroscience education. No study has investigated the additional effects of these interventions in a population with migraine.

The primary aim of this randomized clinical trial will be to determine the effectiveness of a multimodal approach combining manual therapy, exercises, and therapeutic neuroscience pain education on the severity of headache in individuals with migraine. The secondary aims will be to determine its effectiveness on headache frequency (days/month), intensity, pressure pain sensitivity, cervical mobility, and related functions. We will also analyze if there were effects on neck pain-related disability, cutaneous allodynia, kinesiophobia, pain-related catastrophizing, global self-perception of change, and the patient’s quality of life. Thus, we hypothesize that the multimodal physical therapy protocol, which associates multiple interventions with patient education, will help reduce migraine disability, when compared to the application of each intervention alone.

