### Randomization and blinding

Participants will be randomly allocated into three groups: the therapeutic pain neuroscience education (TPNE) group, the manual therapy (MT) group, and the multimodal (MM) group. Randomization will be performed by opening previously enumerated opaque envelopes. Each brown, opaque envelope will contain a paper identifying the group the participant is to be allocated to. This distribution will be made in a sequential order, randomized on Excel® by an external researcher. Randomization will be performed in blocks of 15 envelopes with five of each available group to match the groups’ sample. Two physiotherapists will be responsible for the evaluations. They will be blinded to the treatment allocation group. A physiotherapist will also be responsible for the group interventions and will be blinded to the results obtained in the evaluations.

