### Statistical methods

A descriptive analysis of all variables will be performed, and the data will be reported as mean, standard deviation, and 95% confidence intervals. The statistical analysis will be performed according to the nature and distribution of each variable and be evaluated to verify any changes in the parameters and differences between the groups after the end of the protocol. For the analysis of outcomes, a significance level of 0.05 will be considered.

The intention-to-treat analysis will include all randomized volunteers, regardless of their treatment adherence in the evaluations and analyses [56]. The between-groups comparison will be performed using a mixed-effect regression model for all outcomes, considering the group effect, time effect, and group vs. time interaction. In addition, in those outcomes without predetermined MCID values, it will be calculated based on a distribution-based approach. The clinical relevance of the differences between groups will be classified according to the combination of MCID and effect size (ES), as suggested by Armijo-Olivo et al. [57]. The ES will be estimated by using Cohen’s d. The clinically relevant difference should present a mean difference that is more significant than MCID and ES > 0.4.

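### The 90% power at 21 evaluable per group is that of one unadjusted test; showing multimodal superior to each comparator has about 81% on the same inputs

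*Protocol article*

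**What the plan says.** The trial has three arms: multimodal (MM), manual therapy (MT) and therapeutic pain neuroscience education (TPNE). Allocation is equal: "Randomization will be performed in blocks of 15 envelopes with five of each available group".

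The Sample size section uses a single set of inputs for HIT-6. "It was based on a mean reduction of six points and a standard deviation of 6.03", with alpha 0.05 and power 90%. It concludes: "We estimated 21 individuals per group, and considering a 15% loss to follow-up, 25 individuals per group will be required". It also says: "The standard deviation was derived from a sample of nine volunteers from our database of previous studies". It names no test, no sidedness and no contrast.

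The Background gives the hypothesis that the multimodal protocol "will help reduce migraine disability, when compared to the application of each intervention alone". There are two such interventions, MT and TPNE.

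Statistical methods sets the level ("For the analysis of outcomes, a significance level of 0.05 will be considered") and the model ("The between-groups comparison will be performed using a mixed-effect regression model for all outcomes"), with group, time and group-by-time terms. It mentions no adjustment for multiple comparisons and no rule for combining the two contrasts.

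**The concern.** A hypothesis of superiority over each of two comparators is naturally tested by two contrasts that share the multimodal arm. A sample size with 90% power for one test has less than 90% power for both to succeed. A reader who takes the 90% as the power for the stated hypothesis would think that a truly effective multimodal protocol has a 1-in-10 chance of missing its claim. On the protocol's own inputs the chance is nearer 1 in 5 if both contrasts must be significant. This affects how a non-significant result on either contrast will be read.

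**Working it through.** **Inputs.** From Sample size: difference 6, SD 6.03, alpha 0.05, power 90%, 21 evaluable per arm, 15% loss, 25 randomised per arm. From Randomization and blinding: 1:1:1 allocation. From Background: multimodal better than each single intervention. Assumed: two-sided tests, and 6 points taken as the difference between arms. The two-sided assumption fits; a one-sided calculation gives 18 per group.

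**Step 1: reproduce the plan's figure.** Normal formula for one contrast:

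n = 2 × (1.960 + 1.2816)² × (6.03/6)² = 21.2 per group.

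The protocol's 21 is this value rounded down (rounding up gives 22). Allowing for loss, 21/0.85 = 24.7, so 25 per group.

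**Step 2: power of one test at 21 per group.**

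- Noncentrality: (6/6.03) × √(21/2) = 3.224.
- Normal approximation: Φ(3.224 − 1.960) = Φ(1.264) = 89.7%.
- Noncentral t with 40 df: 88.2%. With variance pooled over three arms (60 df): 88.7%. The two-group t test reaches 89.7% at 22 and 91.0% at 23.
- Three-group F test with one arm differing by 6: the squared deviations of the means (−6, 0, 0) sum to 24, so the noncentrality is 21 × 24/6.03² = 13.86 and power is 91.2% (89.7% at 20 per group). This route also leads to 21.

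On either route, the stated 90% is approximately the power of one test at 0.05.

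**Step 3: power for both contrasts.** With equal arms and a shared multimodal arm, the two test statistics have correlation 0.5. The true advantage is set to 6 points over both MT and TPNE, and each contrast is tested at two-sided 0.05.

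| Method | 21 per arm | 25 per arm |
|---|---|---|
| Pairwise t tests (simulated) | 80.6% | 88.2% |
| t tests, variance pooled over three arms (simulated) | 81.4% | 88.7% |
| Bivariate normal approximation | 82.8% | 89.6% |

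The chance of missing at least one contrast at 21 per arm is therefore 17% to 19%. With no dropout at all, joint power is still just under 90%.

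**Step 4: the alternative reading.** If a win on either contrast were enough, power at 21 per arm would be about 96% with no adjustment. That reading would need control of alpha over the two tests, which the protocol does not describe.

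**The case against.** **The protocol never says that 90% is joint power.** This stands. Quoting power per comparison or for one overall test is common in three-arm trials, and 21 and 25 both reproduce. A reader might infer an arithmetic error, or that the third arm was left out of the calculation. The document supports neither: it names no test, and a three-group F test also gives 21.

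**The rule that both contrasts must succeed is not written down.** This stands in part. The primary aim names no comparator, and the abstract joins the two comparators with "or". But the hypothesis speaks of each intervention, and the Discussion asks whether the approaches work better together than separately. Beating only one comparator would not answer that. The 81% is conditional on this reading and should be labelled so.

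**The 81% is not the power of the planned analysis.** This also stands. HIT-6 is measured at baseline and six later times, and a mixed model is planned. As an illustration, suppose that 6.03 is the SD of raw scores and that baseline is used as a covariate with correlation 0.4. The effective SD is then 6.03 × √(1 − 0.16) = 5.53, and joint power at 21 per arm is about 89%. At correlation 0.5 the SD is 5.22 and joint power about 92%. If 6.03 is the SD of change scores, the gain is smaller. The protocol does not say which it is, and the Sample size section takes no credit for either baseline or repeated measures, so the stated 90% does not rest on them.

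**The SD is itself very uncertain.** True. With nine volunteers, the 95% interval for the SD is about 4.1 to 11.6 under normality, and joint power at 21 per arm runs from about 99% down to about 23% across it. The gap between 90% and 81% is modest beside that. This bears on severity; it does not show which test the 90% describes.

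**Conclusion.** The point holds as a qualified restatement of power. On the protocol's inputs, 21 evaluable per group gives about 88% (t test) for one pairwise contrast and about 81% for multimodal to be significantly better than both MT and TPNE. With all 25 per arm evaluable, the joint figure is about 89%.

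The joint figures rest on four assumptions: that superiority over each intervention needs both contrasts at two-sided 0.05; a true 6-point advantage over each comparator; an SD of 6.03; and single-timepoint t tests. A smaller advantage over either comparator lowers them, and useful baseline or repeated-measures information raises them.

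A reader might also infer that alpha must be split between the two contrasts. Under a rule that both must be significant, it need not be: the overall claim is false if either contrast is null, and that contrast is already tested at 0.05. The shortfall is in power only. The matter is worth correcting in the text, but it does not undermine the design.

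**What to change.** Keep 75 participants. Replace the unqualified 90% in the Sample size section with wording such as:

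> Twenty-one evaluable participants per group give about 88% power for one pairwise comparison at two-sided 0.05, and about 81% power to show multimodal superior to both MT and TPNE (6-point advantage over each, SD 6.03, single-timepoint t tests).

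Add one sentence saying that the claim of superiority over each intervention requires both contrasts to be significant at 0.05, so no alpha split is needed.

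The cost is two sentences and a less favourable stated power. No participant, procedure or analysis changes.

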### Recruitment

Participants will be recruited from the Headache Outpatient Clinic of a university hospital and from the local population through advertisements via social media (Instagram®, Facebook®), and local university radio.

### Randomization and blinding

Participants will be randomly allocated into three groups: the therapeutic pain neuroscience education (TPNE) group, the manual therapy (MT) group, and the multimodal (MM) group. Randomization will be performed by opening previously enumerated opaque envelopes. Each brown, opaque envelope will contain a paper identifying the group the participant is to be allocated to. This distribution will be made in a sequential order, randomized on Excel® by an external researcher. Randomization will be performed in blocks of 15 envelopes with five of each available group to match the groups’ sample. Two physiotherapists will be responsible for the evaluations. They will be blinded to the treatment allocation group. A physiotherapist will also be responsible for the group interventions and will be blinded to the results obtained in the evaluations.

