### Setting

The study will adhere to the guidelines provided by the International Headache Society (IHS) for clinical trials, with respect to the inclusion and exclusion criteria, outcome measures, and statistical analysis. The study protocol has been approved by the local ethics committee (CAAE 36575220.5.0000.5440), and the trial was registered under the access code RBR-7s22c75 in the *Registro Brasileiro de Ensaios Clínicos* (ReBEC) in December 2020. All participants will receive and sign an informed consent form before the beginning of the trial.

The evaluations and interventions will be conducted at the *Hospital das Clínicas* of the Ribeirão Preto Medical School of the University of São Paulo (HCFMRP-USP) and the Laboratory of Evaluation of Posture and Human Movement of the Ribeirão Preto Medical School. The study will include three primary researchers; two will be responsible for data collection, and the third one will be responsible for treatments.

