### Limitations

It should be recognized that this protocol has some limitations. First, patients will be recruited from both tertiary headache centers and the general population. The sample may be composed of cases with distinct severities of migraine. Therefore, there must be a minimum of 3 days of headache per month, and those with concomitant headache diagnoses should be excluded. In addition, due to the greater female preponderance observed in migraine [68], we may have more women than men included in this study. As we will not control for gender distribution among the groups, we cannot guarantee the ability to demonstrate gender differences in the response to treatment. Moreover, the allocation sequence generation and concealment used should guarantee an appropriate randomization process, which avoids the influence of either known or unknown prognostic factors [69].

Second, it will not be possible to blind the participants and the therapist who will apply the interventions, considering the proposed treatment approach. This would increase the risk of bias due to deviation from the intended intervention, affecting mainly the participant’s adherence [69]. According to the Cochrane risk of bias assessment [69], if participants are aware of their assigned intervention, it is more likely that health-related behaviors will differ between the intervention groups. However, the planned interventions of this protocol itself expect different behaviors from the participants (active or passive behaviors). The co-intervention using the prescribed medication is also expected and controlled in the current study by the use of a headache diary. Patients who start a new medical treatment during the trial screening and selection will be recruited to start the study protocol only after 3 months, which is the time required to stabilize the medication’s effects. The patients will be instructed to use only the prescribed medications when appropriate, but the use of non-prescribed medications should also be mentioned separately in the pain diary.

Finally, the results of this trial will be restricted to the immediate effects on most of our variables and mid-term effects on clinical outcomes (headache impact, frequency, and intensity). This was a methodological choice to avoid a higher proportion of dropouts in this trial. However, we prioritized patient-reported outcomes related to migraine.

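### Fixed blocks of 15 leave about 7 of 75 allocations fully deducible by anyone who knows the rule and keeps count: a minor risk that is cheap to reduce

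*Protocol article*

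**What the plan says.** Under Randomization and blinding, the protocol article describes 1:1:1 allocation: "Participants will be randomly allocated into three groups". The device is a set of numbered envelopes: "Randomization will be performed by opening previously enumerated opaque envelopes". The list has an outside author: "This distribution will be made in a sequential order, randomized on Excel® by an external researcher". The block rule is explicit: "Randomization will be performed in blocks of 15 envelopes with five of each available group to match the groups’ sample". The Sample size section sets the total: "Therefore, 75 individuals will be included in this clinical trial".

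On roles, the Setting section says: "The study will include three primary researchers; two will be responsible for data collection, and the third one will be responsible for treatments". Randomization and blinding adds that the two evaluators do not know the arm and that the treating physiotherapist does not see the evaluation results. Limitations accepts that neither the participants nor the therapist can be blinded to treatment. Data collection places randomization after consent, a 30-day diary and the baseline assessment.

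Limitations then says that "the allocation sequence generation and concealment used should guarantee an appropriate randomization process, which avoids the influence of either known or unknown prognostic factors".

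**The concern.** A fixed block size lets past allocations reveal future ones. Here the size and the composition of each block are both written into the protocol. One therapist delivers all three interventions and so learns every allocation. That person can keep the count within each block and knows where each block ends. Near the end of a block, arms drop out of the set of possibilities, and the last envelope is always certain.

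Foreknowledge matters if it reaches someone who can influence when, or in what order, a participant is randomized. The setting is sensitive to this. Recruitment mixes a tertiary clinic with the general population, the article describes no stratification, the primary outcome (HIT-6) is self-reported, and there are 25 per arm.

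As an illustration only, assume that k patients in one arm are replaced by patients whose HIT-6 change differs by 6 points. The arm mean then moves by 6k/25: 0.24 points for k = 1 and 1.2 points for k = 5, against a planned difference of 6. The documents do not show that any such replacement would occur.

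**Working it through.** **Inputs.** Three arms, with blocks of 15 holding five per arm (Randomization and blinding). Total 75, 25 per arm (Sample size).

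**The plan's own figures.** 21/(1 − 0.15) = 24.7, rounded up to 25 per arm; 3 × 25 = 75; 75/15 = 5 complete blocks; 5 × 5 = 25 per arm. The block rule therefore delivers 25/25/25 exactly and has five known ends.

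**Allocations that are certain.** An allocation is certain when every envelope left in the block names the same arm. The expected number per block is the sum, for k = 1 to 5, of the probability that the last k envelopes are all alike:

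1 + 4/14 + (4·3)/(14·13) + (4·3·2)/(14·13·12) + (4·3·2·1)/(14·13·12·11)
= 1 + 0.2857 + 0.0659 + 0.0110 + 0.0010 = 1.36.

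Over five blocks this is 6.8 of 75, or 9.1%.

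**Best guessing.** Let (a, b, c) be the envelopes left per arm and s = a + b + c. Someone who always names the arm with most envelopes left has an expected number of correct guesses of

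E(a,b,c) = max(a,b,c)/s + (a/s)·E(a−1,b,c) + (b/s)·E(a,b−1,c) + (c/s)·E(a,b,c−1), with E(0,0,0) = 0.

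Solved exactly, E(5,5,5) = 7.46 of 15, which is 49.7%. Over five blocks that is 37.3 of 75, against 25 of 75 (33.3%) by chance. The gain is 12.3 allocations, or 16.4 percentage points. By position in the block, the hit rate is 33% at the first envelope, about 51% at the 11th, 64% at the 14th and 100% at the 15th.

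**Other block schemes.** The fixed schemes are exact. The varying schemes are simulated, with sizes equally likely.

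| Scheme | Correct guesses | Certain, of 75 |
|---|---|---|
| Fixed 3 | 61.1% | 25 |
| Fixed 6 | 56.1% | – |
| Fixed 15 (the plan) | 49.7% | 6.8 |
| Varying 9/12/15 | about 50.5% | – |
| Varying 12/15/18 | about 49.0% | about 1.1 |

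For fixed 3, the last envelope of each of 75/3 = 25 blocks is certain. A dash means not needed here. The 1.1 for 12/15/18 assumes a guesser who knows which three sizes are possible but not the order in which they were drawn. If the drawn sizes became known, each block would again end in about 1.36 certain allocations and most of the gain would be lost. Withholding the structure is therefore essential.

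**The case against.** The case for leaving the plan alone is substantial, and most of it stands.

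- **The large figure overstates the exposure.** A reader might infer that half of the allocations are known in advance. They are not: one third would be guessed by chance, the gain is about 16 points, and only 9% are certain.
- **Knowledge and opportunity are separated on paper.** A reader might infer that the therapist could hold a severe patient back for a preferred slot. That needs one person, or a leak between persons, combining the count, the patient's severity and control of entry. The evaluators do not know the arm, the therapist does not see the evaluations, and the article gives the therapist no part in recruitment or in opening envelopes.
- **Custody of the envelopes is not stated.** A reader might infer that the treating team opens them. The article does not say so, and an article commonly leaves this to the full protocol. No finding is based on that silence.
- **Publication adds nothing that can be shown.** The document gives no publication date, so use of the printed block size by outsiders during recruitment cannot be established.
- **Fifteen is already a large block for three arms.** Smaller blocks are worse, and varying the size at or below 15 does not lower the average guess rate. Fixed blocks also secure equal arms, which is their stated purpose.

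The objection does not remove the stated rule itself: known block ends, a team member who can keep the count, and about seven allocations that follow with certainty.

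**Conclusion.** The point holds as a minor design weakness. For someone who knows the block rule and every past allocation, 6.8 of 75 allocations (9%) are fully determined and 49.7% can be guessed, against 33.3% by chance. The assurance quoted from Limitations is too strong for that procedure.

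These figures assume complete knowledge of the count and strict use of the numbered sequence. They measure predictability, not bias. The documents do not show that a prediction would reach a person able to act on it, and the existing blinding of evaluators and therapist makes that less likely. The sample size is unaffected.

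**What to change.** 1. Have the external researcher who already generates the list draw block sizes at random from a set that is not entirely below 15, for example 12, 15 and 18.
2. Withhold the block structure from the three researchers. The version of the protocol they use should say only that blocks vary in size.
3. Have the external researcher release each allocation, in strict sequence, once that participant's baseline assessment is recorded.
4. If fixed blocks of 15 are kept, reword the sentence in Limitations so that it describes the safeguards without guaranteeing their result.

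Steps 1 to 3 reduce certain allocations from about 6.8 to about 1 of 75. They should not be presented as lowering the average guess rate, which stays near 49%.

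The cost is one new list and 75 release messages, handled by someone already involved. The downside is that the last block may be incomplete, so arms can end a few participants away from 25. With 12/15/18 the deviation cannot exceed 4: the worst case is an unfinished block of 18 whose first six entries all fall in one arm, 6 − 2 = 4, or whose first twelve all miss one arm, 4 − 0 = 4.
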